#### 9.5.2 MAJOR SECONDARY ANALYSES

The number of participants is reported, who achieve a SLE responder index of 4 (SRI-4) upon daratumumab treatment at Week 12 (primary endpoint visit), i.e. 4 weeks after the last daratumumab injection. Descriptive statistics will be used to report the clinical efficacy parameters, the patient reported outcome measure SF-36 and serological efficacy parameters at each assessment. The change in efficacy parameters, patient reported outcomes will be calculated along with 95% confidence intervals.

Disease flares are defined by the SELENA-SLEDAI flare index. The time to flare during the study will be analyzed by Kaplan-Meier analyses. The need for next treatment to control the disease within the 6-months follow-up is also be analyzed by Kaplan-Meier analyses. The TEAE will be documented during daratumumab treatment. The incidence and the incidence rate per 10 treatment months of adverse events will be calculated. The incidence of serious adverse events will be separately reported.

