| 
Analysis of efficacy:
(cont.)
                   | 
 
• Proportion of subjects with a SLE responder index of 4 (SRI-4); Time frame: up to Week 36 in the core study and up to Week 84 in the LTE observational period.
 
• Proportion of subjects that meet the Lupus Low Disease Activity State (LLDAS) response criteria by visit.
 
• Change from baseline in Systemic Lupus Erythematosus Disease Activity Index 2000 (SLEDAI-2K) scores by visit.
 
• Change from baseline in physician global assessment (PGA), a scale ranging from 0-3, by visit.
 
• Change from baseline in CLASI (Cutaneous Lupus Erythematosus Disease Area and Severity Index), CDAI (Clinical Disease Activity Index) and proteinuria (urinary protein/creatinine ratio, UPCR), by visit.
 
• Time to first flare (SELENA-SLEDAI flare index, SFI).
 
• The daily prednisolone (or equivalent) dosage, by visit between Week 12 and Week 36 in the core study and up to Week 84 in the LTE observational period.
 
• Time to new treatments to control SLE activity, by visit.
 
 
4. To evaluate whether daratumumab treatment is associated with improvement of health-related quality of life, the following outcome measures will be performed:
 
 
• Change from baseline in Health-related quality of life (HR-QoL), measured by SF-36 score.
 
• Change from baseline in Functional Assessment of Chronic Illness Therapy (FACIT)-Fatigue score.
 
 
Additional endpoints of the core study and LTE observational period
 
1. Immunologic changes (pharmacodynamics) following daratumumab treatment will be evaluated as follows:
 
 
• Change from baseline in number and phenotype of peripheral blood plasmacytoid dendritic cells (pDC), natural killer (NK) cells, CD4+ and CD8+ T cells, CD19+ B cells and CD19+CD20negCD27high plasmablasts, by visit.
 
• Change from baseline in interferon type I activity
 
• Change from baseline in gene expression profile and antigen receptor repertoire on peripheral blood T and B cells.
 
 |

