## 1.5 PERIOD AND TIMELINES

Treatment period: 8 weeks

Primary endpoint: at Week 12

Follow-Up Period in the core study period: 28 weeks

Total study duration per subject in the core study period: 40 weeks (4 weeks screening, 8 weeks treatment, 28 weeks follow-up)

First patient first visit to last patient first visit: 15 months

Follow-up in the long-term extension (LTE) observational period: 48 weeks

Total study duration: 88 weeks (40 weeks in the core study and 48 weeks in the LTE observational period)

Interim analysis: after the 5th patient at Week 12

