- The daily prednisolone (or equivalent) dosage, by visit between Week 12 and Week 36. Time frame: baseline, and follow-up visits of the core study period at Week 3, 5, 7, 9, 12, 16, 20, 24, 28, 32, 36, and each follow-up visit of the LTE observational period.  
Time to new treatments to control lupus activity will be investigated. Time-frame: baseline, and follow-up visits of the core study period at Week 3, 5, 7, 9, 12, 16, 20, 24, 28, 32, 36, and at Week 42, 48, 54, 60, 66, 72, 78 and 84 of the LTE observational period.

4. To evaluate whether daratumumab treatment is associated with improvement of health-related quality of life, the following outcome measures will be performed:

- Change from baseline in Health-related quality of life (HR-QoL), measured by SF-36 score, time frame: up to Week 36. The 36-Item Short Form Health Survey questionnaire (SF-36), a validated instrument widely used to evaluate Health-Related Quality of Life SLE, by visit. Time frame: baseline, and follow-up visits of the core study period at Week 3, 5, 7, 9, 12, 16, 20, 24, 28, 32, 36, and at Week 42, 48, 54, 60, 66, 72, 78 and 84 of the LTE observational period.
- Change from baseline in Functional Assessment of Chronic Illness Therapy (FACIT)-Fatigue score. Time frame: up to Week 36. The FACIT-Fatigue scale includes 13-fatigue related questions for subject rates fatigue during the previous 7 days, yielding on overall score 0 to 52, with lowest score representing worst fatigue, by visit. Time frame: baseline, and follow-up

visits of the core study period at Week 3, 5, 7, 9, 12, 16, 20, 24, 28, 32, 36, and at Week 42, 48, 54, 60, 66, 72, 78 and 84 of the LTE observational period.

- Change from screening in the number of organs with damage according to the SLICC Damage Index (SDI) measured at the final visit at Week 84

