#### 6.4.1 GLUCOCORTICOID THERAPY

The use of glucocorticoids for the indication SLE is allowed to a maximum of 20mg daily prednisolone (or equivalent) throughout the study. The glucocorticoid dosage must be stable from baseline until Week 12 (primary endpoint study visit). After Week 12 (primary endpoint visit), it is possible to reduce the glucocorticoid dosage if the disease activity allows tapering, according to the judgment of the treating physician.

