### 6.5 RESCUE MEDICATION

For the treatment of disease flares, defined according to the SLEDAI-flare index (SFI), administration of glucocorticoids is allowed up to a maximum dose of 100mg/day. In case of recurring flares or ongoing disease activity, defined as a state of not achieving low disease-activity (LLDAS), administration of additional disease-modifying drugs is allowed from Week 12 (primary endpoint visit) (except for medications listed in section 6.6 PROHIBITED THERAPIES).

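### The Kaplan-Meier analysis of need for next treatment stops at an unanchored six months, although the endpoint is defined from baseline to Week 84

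*Protocol*

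**What the plan says.** Section 3.2.3, which covers the endpoints of both periods, states: "Time to new treatments to control lupus activity will be investigated". The time frame attached to it begins at baseline, runs through the core visits to Week 36, and continues "and at Week 42, 48, 54, 60, 66, 72, 78 and 84 of the LTE observational period". The synopsis lists the same endpoint under the secondary endpoints of both periods: "Time to new treatments to control SLE activity, by visit".

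The only time-to-event analysis given for it is in section 9.5.2: "The need for next treatment to control the disease within the 6-months follow-up is also be analyzed by Kaplan-Meier analyses". No start point is given for the six months. The sentence before it analyses time to flare by the same method over the study, with no six-month limit.

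Section 1.5 gives 8 weeks of treatment and 28 weeks of core follow-up, and then: "Follow-up in the long-term extension (LTE) observational period: 48 weeks". Section 6.5 says of rescue that "administration of additional disease-modifying drugs is allowed from Week 12 (primary endpoint visit".

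**The concern.** An endpoint and its analysis should cover the same period. Here the endpoint runs to Week 84 and the analysis ends at a point that cannot be located on the visit schedule. Two analysts could choose different cut-offs, and in an open-label trial that choice could be made after the data are seen.

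The drug is given for eight weeks, so how long patients manage without a new lupus treatment is a natural descriptive measure of durability. Because section 6.5 opens additional disease-modifying drugs only from Week 12, much of the information on that type of event comes after Week 12. A cut at about six months leaves most of that period off the curve. A patient who first needs a new drug at Week 48 would appear only as censored at the cut-off.

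**Working it through.** **The plan's own durations.** Core: 4 + 8 + 28 = 40 weeks. LTE: 84 − 36 = 48 weeks, which equals 8 visits × 6 weeks. Total: 40 + 48 = 88 weeks, as section 1.5 states.

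**Day scale.** The schedule puts Week 1 at Day 0 and Week 12 at Day 77, so Week w is Day 7(w − 1). Extending this rule, Week 84 is Day 581. For Week 36 the rule gives Day 245; the schedule prints Day 241. Six months is taken as 6 × 30.4375 = 182.6 days.

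**Share outside the curve.** The window from Week 12 to Week 84 is 581 − 77 = 504 days, or 72 weeks. Share left out = (581 − cut-off day) / 504.

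| Reading of the six months | Cut-off day | Approx. week | Share of Weeks 12–84 left out |
|---|---|---|---|
| From baseline (Day 0) | 182.6 | 27 | 398.4/504 = 79% |
| From last dose (Day 49) | 231.6 | 34 | 349.4/504 = 69% |
| From Week 9 (Day 56) | 238.6 | 35 | 342.4/504 = 68% |
| Core follow-up to Week 36 | 245 | 36 | 336/504 = 67% |
| From Week 12 (Day 77) | 259.6 | 38 | 321.4/504 = 64% |

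Using the printed Day 241 for Week 36 gives 340/504 = 67.5%, so the discrepancy does not matter here. Measured over the whole period from baseline to Week 84, the share left out runs from 321.4/581 = 55% to 398.4/581 = 69%.

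**Visits.** After Week 12 there are 14 visits: six in the core study (Weeks 16 to 36) and eight in the LTE. A Week 36 cut keeps six. A cut six months from baseline keeps three (Weeks 16, 20 and 24).

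**Which reading is likeliest.** Core follow-up of 28 weeks is 196/30.4375 = 6.4 months, so the phrase most plausibly means follow-up to Week 36 and was not updated when Amendment 1 added the LTE. That is an inference; the mismatch with section 3.2.3 does not depend on it.

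**Illustration under assumptions.** The protocol gives no event rate. Assume 10 patients, no dropout, and a constant hazard from Week 12 with a median time to new treatment of 6 to 24 months. A Week 36 cut then captures 4.7 of 8.5 expected events at a 6-month median and 1.5 of 3.8 at a 24-month median, so 45% to 61% are lost.

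**The case against.** The strongest reply is that this is a one-phrase mismatch in a secondary, descriptive endpoint with 10 patients, and that the later information is reported elsewhere. Much of that stands. Section 9.1.6 summarises new SLE medications and dose changes at each study visit and lists patients with increases, and concomitant therapy is recorded at every LTE visit. Section 7.3.4 counts a new systemic immunosuppressant, an added antimalarial or NSAID, or a prednisone increase for SLE activity as a flare, and the flare curve is not cut at six months. Neither replaces the defined endpoint, however. Visit-wise summaries do not handle censoring, and a first flare can be triggered by symptoms or a score change without any new treatment.

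A reader might infer stronger points that the documents do not support:

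- **That the truncation makes the drug look more durable.** It does not. A patient first treated at Week 48 really is event-free at six months, and censoring at a fixed cut-off does not bias the estimate up to that point. The curve is shorter, not inflated.
- **That the curve opens with about 11 weeks that must be event-free.** The Week 12 opening concerns additional disease-modifying drugs. For flares, section 6.5 also says "administration of glucocorticoids is allowed up to a maximum dose of 100mg/day" and gives no start week. Section 7.2.3 permits otherwise prohibited drugs in severe cases, also with no start week. Section 8.2 foresees a permitted immunomodulator being started, under its rules on discontinuing study drug. Early events are possible.
- **That the clock should therefore start at Week 12.** That would contradict the baseline start in section 3.2.3, take early failures out of the curve, and sit badly with the intention-to-treat principle in section 9.3.
- **That this is the question the LTE was added to answer.** The primary objective of the LTE is safety (section 3.1.4), and the efficacy measures named in section 3.1.5 do not include time to new treatment.

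**Conclusion.** The point holds as an inconsistency within the current protocol. The stated Kaplan-Meier analysis covers only part of the period over which sections 3.2.3 and the synopsis define the endpoint, and its cut-off has no origin. On the likeliest reading, 67% of Weeks 12 to 84 and all eight LTE visits fall outside the curve; across the readings examined the range is 64% to 79%. These figures assume the schedule's day rule continues through the LTE and that patients remain under observation to Week 84. LTE entry needs separate consent (section 5.3), so the follow-up actually gained may be smaller.

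The consequence is a missing description of later durability, not a biased estimate. No error rate or sample size depends on this endpoint. The change is worth making because it is specific and nearly free.

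**What to change.** In section 9.5.2, replace the six-month limit with: *from baseline up to Week 84, censored at last contact for patients who do not enter or complete the LTE*. Read the Week 36 estimate from the same curve and report it as the core-study figure.

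Keep baseline as the time origin and count starts before Week 12 as events. When interpreting the curve, note that section 6.5 opens additional disease-modifying drugs only from Week 12, so its early part partly reflects that restriction.

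The cost is one sentence of wording. No visits, data or patients are added, and no treatment rule changes. The drawback is precision: with 10 patients, some of whom may be censored at Week 36, the tail should be shown with numbers at risk and read cautiously.

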### 9.6 PHARMACODYNAMIC AND BIOMARKER ANALYSES

The number and phenotype of peripheral blood immune cell subsets will be assessed using multicolor flow cytometry. Descriptive statistics will be used to report the biomarker at each assessment. The change in efficacy parameters will be analyzed by linear mixed models.

### 9.7 PHARMACOKINETIC ANALYSES

The daratumumab concentration will be investigated after the end of the study from cryopreserved serum samples obtained at 1 week after the last daratumumab injection, i.e. Week 9, provided that

the primary endpoint is achieved, and at study entry in the LTE observational period. Descriptive statistics will be used to report the study drug concentration.

## 9.8 SAFETY ANALYSES

Safety analyses will include summaries of discontinuations, deaths, AEs, and SAEs. Targeted safety events in SLE, based on mechanistic plausibility (e.g. serious infections, opportunistic infections, TB, hypersensitivity reactions) or potential population risks (e.g. worsening of renal or CNS disease) will also be summarized.

### 9.8.1 ADVERSE EVENTS

The verbatim terms used in the CRF by Investigators to identify adverse events will be coded using the most recent version of Medical Dictionary for Regulatory Activities (MedDRA). Treatment-emergent adverse events are adverse events with onset during the treatment phase or that are a consequence of a pre-existing condition that has worsened since baseline. All reported adverse events will be included in the analysis. The incidence and incidence rate will be summarized on System Organ Class (SOC) and Preferred Term (PT) level. The incidence, severity, and types of infections, infusion reactions, and injection-site reactions will be analyzed for this study. Summaries, listings, datasets, or subject narratives may be provided, as appropriate, for those subjects who die, who discontinue treatment due to an adverse event, or who experience a severe or a serious adverse event.

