### 3.2.2 PRIMARY ENDPOINT OF THE LTE OBSERVATIONAL PERIOD

1. Safety will be investigated by reporting the proportion of participants with treatment emergent adverse events (TEAE) by severity and SAEs through EOS. Routine safety evaluations include AE monitoring, physical examinations, vital sign measurements, ECGs, and clinical laboratory testing (hematology, chemistry, and urinalysis) as a measure of safety and tolerability for the entire study duration. Time frame: each visit.

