### 3.2.3 SECONDARY ENDPOINTS OF THE CORE STUDY AND LTE OBSERVATIONAL PERIOD

1. Safety will be investigated by reporting the proportion of participants with treatment emergent adverse events (TEAE) by severity and SAEs through EOS. Routine safety evaluations include AE monitoring, physical examinations, vital sign measurements, ECGs, and clinical laboratory testing

(hematology, chemistry, and urinalysis) as a measure of safety and tolerability for the entire study duration. Time frame: each visit.

SAEs will be assessed at any dose that results in a death, inpatient hospitalization or prolongation of existing hospitalization, persistent or significant disability/incapacity, or a congenital anomaly. The following areas of safety interest will be routinely assessed to identify any major safety findings related to immunosuppression or potential risks associated with the individual classes of therapy:

- serious and/or opportunistic infections, herpes zoster, active TB, malignancies (all types), adjudicated gastrointestinal (GI) perforations, adjudicated cardiovascular events (e.g., major adverse cardiovascular event [MACE]), anemia, neutropenia, lymphopenia, renal dysfunction, hepatic disorders, and adjudicated embolic and thromboembolic events (non-cardiac, non-central nervous system [CNS]) including venous thrombotic events defined as pulmonary embolism and deep vein thrombosis and clinical laboratory testing (hematology, chemistry, and urinalysis) as a measure of safety and tolerability for the entire study duration.

2. To investigate the effect of daratumumab on serologic changes, the following secondary endpoints are defined:

- Change from baseline in serum levels of anti-dsDNA antibodies, immunoglobulins (IgM, IgG and IgA), antinuclear antibodies (ANA) and extractable antinuclear antibodies (ENA), such as anti-Smith, anti-Ro (SSA), anti-La (SSB), anti-ribonucleoprotein (RNP) and anti-phospholipid antibodies, rheumatoid factor (RF) and anti-citrullinated peptide antibodies (ACPA) (if present) by visit. Time frame: baseline, and follow-up visits of the core study period at Week 3, 5, 7, 9, 12, 16, 20, 24, 28, 32, 36, and at Week 42, 48, 54, 60, 66, 72, 78 and 84 of the LTE observational period.

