## 4 TRIAL DESIGN

### 4.1 STUDY SETTING

This is a phase 2 monocenter, open label, Proof-of-Concept (PoC) study. A target of 10 participants with moderate to severe SLE will be enrolled in the study.

Screening Period: 28 days

Treatment Period: 8 weeks

Study type: interventional, open-label, uncontrolled

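### The treatment-emergent definition stops at the 8-week treatment phase, so the extension's primary safety endpoint cannot count late, new, non-serious events as TEAEs

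*Protocol*

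**What the plan says.** The definition in section 9.8.1 has two routes. The first goes by onset and is tied to the treatment phase: "Treatment-emergent adverse events are adverse events with onset during the treatment phase". The second route has no end date and takes in events that start at any time: "or that are a consequence of a pre-existing condition that has worsened since baseline". The same section adds: "All reported adverse events will be included in the analysis".

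Section 9.5.2 repeats the time limit for reporting: "The TEAE will be documented during daratumumab treatment". The next sentence sets the rate: "The incidence and the incidence rate per 10 treatment months of adverse events will be calculated".

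The length of treatment is fixed in section 4.1 ("Treatment Period: 8 weeks") and repeated in 1.5 and 4.4, where the core follow-up (28 weeks) and the extension (48 weeks) are listed as separate periods.

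The primary objective of the extension is long-term safety (3.1.4). Its primary endpoint (3.2.2) is to be assessed by "reporting the proportion of participants with treatment emergent adverse events (TEAE) by severity and SAEs through EOS", with every visit as the time frame. Section 3.2.3 uses the same endpoint as the first secondary endpoint for both periods, and the synopsis repeats it. Section 10.5 has all AEs recorded from consent to the last follow-up visit.

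**The concern.** The endpoint is meant to describe safety up to Week 84, but its main component is defined by onset in a phase that ends at Week 8. An analyst who applies 9.8.1 literally would leave out of the TEAE count a new non-serious infection or cytopenia first seen in the extension, unless it was judged to follow from a worsened pre-existing condition. The same holds for the 28 weeks between treatment and extension. Another analyst, relying on the words about end of study in 3.2.2, would count it. Both could claim to follow the protocol, and they would report different values for the primary endpoint of one of the trial's two periods.

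The rate in 9.5.2 adds a second uncertainty. Its denominator is treatment time, while 9.8.1 brings in all reported AEs, so the text does not guarantee that events and person-time come from the same period.

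**Working it through.** **Inputs** (Protocol 1.5, 4.1, 4.4, 6.2.4 and the time and events schedule): screening 4 weeks; treatment 8 weeks, last dose at Week 8 (Day 49); core follow-up 28 weeks; extension Weeks 36 to 84, with 8 visits every 6 weeks.

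**Reproducing the protocol's own timeline.** Core: 4 + 8 + 28 = 40 weeks. Total: 40 + 48 = 88 weeks. Extension: 8 × 6 = 48 = 84 − 36. All agree with sections 1.5 and 4.4.

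**Gap from last dose to extension entry.**
- By week labels: 36 − 8 = 28 weeks.
- By the day row: 241 − 49 = 192 days; 192 / 7 = 27.4 weeks, or 26.4 to 28.4 with the ±7-day window.
- The spacing of the other visits, 7 × (week − 1), would put Week 36 at Day 245 rather than Day 241. The gap is then exactly 28 weeks, so the conclusion does not change.

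**Coverage of the onset route.**
- Extension: the treatment phase ends at Week 8 and the extension starts at Week 36, so the overlap is 0 of 48 weeks.
- Core follow-up: 0 of 28 weeks.
- Whole post-baseline period: 8 / 84 = 9.5%.

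**Can the treatment phase be read to include follow-up?** No. Sections 1.5 and 4.4 list treatment, follow-up and extension separately, sections 7.1 and 8.2 speak of a follow-up phase, and 9.5.2 ties TEAEs to the time on daratumumab.

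**What is counted in the extension (Weeks 36 to 84) under the text as it stands.**

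| Event first seen in the extension | TEAE? | SAE part of endpoint? | All-AE analysis (9.8.1)? |
|---|---|---|---|
| New, non-serious, not from a worsened pre-existing condition | No | No | Yes |
| Follows from a worsened pre-existing condition, non-serious | Yes, second route | No | Yes |
| Meets an SAE criterion | Only by second route | Yes | Yes |

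The first row is the gap. Section 10.7 shows that it can contain important events: an event of special interest, such as a Grade 4 cytopenia, is serious only if it meets the SAE definition.

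**The cumulative reading.** If end of study means a running total from first dose, TEAEs from Weeks 1 to 8 carry forward. The TEAE proportion at Week 84 then mainly repeats the treatment phase and can rise later only through the second route.

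**The case against.** The strongest reply has four parts.

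1. *The definition has two routes.* The worsening route has no end date and every participant enters with active SLE, so events caused by a later worsening of lupus can be TEAEs in the extension. This stands.

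2. *The endpoint has two components.* SAEs through end of study are not limited to treatment-emergent events, so serious late infections, malignancies or cytopenias are counted. This stands too. A reader might infer that the endpoint is almost empty, or that near-zero incidence will be reported whatever happens. The text does not support that, because the second route and the SAE component both reach Week 84.

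3. *Nothing is lost.* AEs are collected to the last visit (10.5), all of them enter the analysis (9.8.1), and targeted safety events are summarised (9.8). This is correct. The gap lies in the endpoint definition and not in the data. But an all-AE table beside the endpoint does not repair the endpoint.

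4. *The rate may be consistent.* In 9.5.2 the rate follows directly on TEAEs documented during treatment, so events and person-time can be read as covering the same weeks. A reader might instead divide all events to Week 36 or Week 84 by treatment time and infer an inflation of 36 / 8 = 4.5-fold or 84 / 8 = 10.5-fold. No section instructs this. Those factors hold only on that reading, with a constant event rate, full follow-up and, for the second, all 10 patients completing the extension. The sample-size section assumes 50% drop-out and the extension needs its own consent, so they are conditional upper bounds and not results of the plan.

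The shorter SAE list in 3.2.3 ("SAEs will be assessed at any dose that results in a death, inpatient hospitalization or prolongation of existing hospitalization", and so on) leaves out life-threatening events, suspected transmission of an infectious agent and medically important events, all of which 10.1.3 includes. That is a separate, minor inconsistency. Section 10.7 points to 10.1.3 for the SAE definition and 3.2.2 contains no list of its own, so it does not show that the extension's SAE component is narrowed.

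**Conclusion.** The TEAE definition in 9.8.1, read with 9.5.2, does not fit the endpoint in 3.2.2 and 3.2.3. This is not a detail left to the statistical analysis plan: the protocol states a definition and an endpoint that disagree.

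The onset route covers 0 of 48 extension weeks and 0 of 28 core follow-up weeks. What falls out is a specific class of event: new in onset, non-serious, and not the result of a worsened pre-existing condition. For that class the primary endpoint of the extension is blind, although the objective is long-term safety.

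The conclusion rests on two readings: that the treatment phase is the 8-week treatment period, and that the second route is applied as written, with no end date. It needs no assumption about event rates, and the size of any under-count cannot be given in advance. The study is small, uncontrolled and descriptive, which limits the consequence, but the endpoint as defined would still misdescribe late safety.

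**What to change.** Choose one definition and use it in the synopsis, 3.2.2, 3.2.3, 9.5.2 and 9.8.1:

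- either define a TEAE as any AE that starts or worsens between the first dose and the last study visit (Week 36, or Week 84 for participants in the extension);
- or keep the treatment-phase definition for TEAEs and define the extension's primary endpoint on all AEs with onset from extension entry to Week 84. The core safety endpoint in 3.2.3 then needs a matching statement for the 28-week follow-up.

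In both cases, report events separately for treatment, core follow-up and extension. Replace the rate per 10 treatment months with a rate per person-time observed in the period in which the events are counted. Remove or amend the sentence in 9.5.2 that confines TEAEs to the time on daratumumab.

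As a separate tidy-up, replace the SAE list in 3.2.3 with a reference to 10.1.3.

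The cost is an amendment to wording. AEs are already recorded to the last visit under 10.5, so no new data, visits or procedures are needed.
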